### Data Collection and Management

Data collection will be carried anonymously on REDCap, an online-based software for the design of databases. This will allow for higher quality and robustness of the data collected and a reduction of missing data.

Data will be collected in a pseudo-anonymized way, attributing a record ID to each patient on the electronic database and saving the correspondences between names and identification codes on a separate document that will be destroyed at the end of the study.

### Statistical Analysis

Statistical analyses will be performed using SPSS 27.0 software (IBM SPSS, Chicago, Illinois, USA). Descriptive statistics of variables belonging to the four clinical assessment categories (clinical and nursing complexity, neurological profile, functional evaluation and neurophysiological parameters, and methylation levels of the BDNF gene) will be provided for each time point. The statistics will include absolute counts and relative frequencies for categorical and dichotomous variables, whereas numeric variables will be reported as mean and SD or median and interquartile range, according to the normal or nonnormal distribution. The violation of the normality assumption will be ascertained using the Shapiro–Wilk test.

Variable comparisons at two-time points will be performed by paired *t*-test or Wilcoxon signed-rank test for numeric scales, as appropriate for the normality of the data, and by the McNemar test for paired categorical or dichotomous data. For those variables evaluated at all time points, differences over time will be ascertained using a repeated measures ANOVA (Bonferroni and Sheffé corrections will be applied to multiple comparisons) or a Friedman test, for continuous variables, and a Cochran's *Q* test for dichotomous variables. In all the above-mentioned analyses, a *p*-value <0.05 will be considered as statistically significant.

For what concerns the primary outcome, those variables identified through univariate analysis as recovery predictors on the GOS-E scale will be grouped in categories based on the nature of variables: clinical or nursing complexity (including anagraphical data), neurological profile, functional factors, neurophysiological parameters, and genetic profile. For each category, a multiple logistic regression analysis will be conducted to investigate whether there is a relationship with the primary outcome. The analysis will be then repeated including variables from different categories that showed a significant association with the functional recovery at discharge. For the secondary outcomes, a two-step process constituted on univariate analyses adjusted by age and sex and multivariate analysis will be performed. More in detail, univariate analyses, adjusted by proper confounders, and multivariate analyses will be performed using logistic regressions.

A further step will involve advanced machine learning methods for the short- and long-term prediction of outcomes. Classical solutions such as linear and logistic regression will be compared with solutions based on support vector machines, random forests, or multilayer perceptrons and also with “deep” artificial neural networks (convolutional neural networks, recurrent neural networks, and ensemble learning solutions). The performances of different algorithms in predicting recovery outcomes will be compared in terms of accuracy, F1-score, root mean square error, and determination coefficient. The effect of hyperparameter tuning and automatic features selection strategies will also be tested by nested crossvalidation, with the final aim to quantify the solution generalization capability when applied to new patients who were not included in model definition and training.

To assess the clinical applicability of these solutions, the prediction of recovery milestones by automatic methodologies will be compared to the evaluation of a multidisciplinary team, which will be kept blind with respect to the algorithm outputs. This assessment is usually performed in clinical practice approximately 2 weeks from admission to inform the caregivers of the patients' expected recovery path. Opinions by both single professionals and the full consensus will be compared to the automatic tool predictions.

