## Introduction

Severe acquired brain injury (sABI) is characterized by traumatic, anoxic, vascular, or other brain damages that cause coma for at least 24 hand frequently lead to permanent sensorial, motor, cognitive, or behavioral disabilities. The incidence rate of sABI patients is estimated between 10 and 15 new cases/100,000 persons/year and the prevalence rate between 300 and 800 cases /100,000 persons, which represents comprehensively about 150,000 persons in 2016 in Italy (1, 2).

After sABI, some patients may survive in a state of prolonged disorder of consciousness (DoC) (3), a condition that encompasses (1) unresponsive wakefulness syndrome (UWS), in which the eyes are open, but there is no evidence of voluntary behaviors and (2) minimal consciousness state (MCS), an intermediate state in which minimal, inconsistent but reproducible behavioral signs of responsiveness are present (4). Based on the complexity of patients' behavioral responses, a subcategorization of MCS patients was proposed (5); namely, “MCS minus” (MCS–) characterizes patients with intentional low-level behavior, such as visual search or localized motor response to nociceptive stimulus, and “MCS plus” (MCS+) indicates patients with high-level behavioral interactions, such as execution of simple verbal commands (5). In some cases, patients recover full consciousness, as marked by the regaining of functional and reliable “yes/no” communication (emergence from MCS, E-MCS), but they may still present severe motor and cognitive or behavioral impairments persisting lifelong.

Besides the severity of the neurological state, patients with sABI frequently present a high clinical complexity characterized by very frequent comorbidities (6) and medical complications (7), which can further impact clinical improvement and survival. Although late consciousness recovery and progression have been reported in patients with UWS or MCS (8), long-term mortality is high (42–52%) in patients with prolonged DoC (1, 2), and survivors frequently show severe to extremely severe outcomes (9).

Younger age, shorter postevent time, and traumatic etiology have been identified as the possible clinical predictors of short-term consciousness recovery in patients with prolonged DoC (10).

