### Data Collection

The multiprofessional staff (i.e., neurologists, neurophysiologists, physiatrists, internists, neuropsychologists, neurophysiological technicians, nutritionists, physiotherapists, speech therapists, occupational therapists, and nurses) of each center will gather clinical and neurophysiological data and structural indices of overall brain damage from brain imaging. To promote a training on specific datasets, the coordinating center will schedule meetings with all the involved users, before the starting of the enrollment, to guarantee homogeneity of data collection. For the analysis of genetic or epigenetic markers, in the presence of signed informed consent, a blood sample will be collected from each patient along with the routine blood drawn at T0, T1, and T2, frozen and later transported to the Neurogenetics Laboratory of Careggi Hospital, in Firenze.

Measures will be taken at (1) inpatient rehabilitation admission (T0), (2) 3 months from T0 (T1), (3) 6 months from T0 (T2), (4) 12 months from the acute event (T3), and (5) 24 months from the acute event (T4). The timeline of the study is illustrated in Figure 1.

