
After regaining consciousness, patients with sABI often present many factors that may limit their recovery. Indeed, significant neurological impairments, including motor deficits, myoclonus, dystonia, movement disorders, aphasia, neglect, abulia, impairments in attention, memory, executive functions, mood disorders, and epileptic seizures, may have a dramatic impact on the level of functional independence and quality of life (51). Also, sABI patients frequently present a high clinical complexity, with a high rate of comorbidities (6) and medical complications (7) that can further compromise the functional prognosis. For their complex nature, patients with sequelae of sABI require several assessment instruments to correctly quantify every residual symptom and adequately reflect their clinical state during the acute, postacute, and community-living sABI phase. Furthermore, given the long duration of the rehabilitation process and the continuous evolution of patients over time, the measurement of outcomes also needs to be dynamic, to accurately depict, as realistically as possible, the patient's situation at each time point. Recently, the Italian Society of Physical and Rehabilitation Medicine proposed a minimum assessment protocol for post-sABI patients (52); however, there is no National Health System (NHS) requirement as to the measures of sABI rehabilitation outcomes. In this study, evaluation tools were chosen in accordance with the Italian Society of Physical and Rehabilitation Medicine minimum assessment protocol (52), and targeted outcome measures were hierarchically organized based on the patient's state of consciousness. Only after the consciousness recovery, some measures of functioning, including motor and cognitive impairment, activity, and participation were applied. Further, special attention was given to the care burden (the presence of compliances and comorbidities, the presence of medical devices, oral/artificial feeding, and communication capabilities) to assess the impact, on both the caregiver and the NHS, at discharge and until 24 months after the acute event.

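### Change across the five visits is tested only in patients with every visit, so this secondary, descriptive analysis describes 24-month completers and ignores the varying T2–T3 interval

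*Protocol article*

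**What the plan says.** The Statistical Analysis section of the protocol article sets a rule by type of variable. "For those variables evaluated at all time points", it says, "differences over time will be ascertained using a repeated measures ANOVA" or a Friedman test if the variable is continuous. Cochran's Q is the "test for dichotomous variables". The threshold for these comparisons is a p-"value <0.05 will be considered as statistically significant", and "Statistical analyses will be performed using SPSS 27.0 software".

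Table 1 shows which variables fall under the rule, that is, those marked at T0, T1, T2, T3 and T4: CRS-R, GOS-E, FOIS, body mass index and presence of medical devices.

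On timing, Data Collection counts T1 and T2 from admission to rehabilitation (3 and 6 months) and the later visits from injury: "4) 12 months from the acute event (T3), and (5) 24 months from the acute event (T4". The inclusion criteria allow admission at any time under 4 months from injury. T3 and T4 are telephone interviews.

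On survival, the Introduction states that "long-term mortality is high (42–52%) in patients with prolonged DoC". The article does not say how deaths or missed visits enter the three tests. Its only remark on missing data is that the electronic database should reduce them.

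**The concern.** Repeated-measures ANOVA in its classical form, Friedman and Cochran's Q all work on a complete patient-by-visit table. With five visits, one empty cell removes the patient's whole row. Someone who dies at 15 months has observed values at T0, T1, T2 and T3, and none of them is used.

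The cohort is one in which death before 24 months is expected, and it is plausible that patients who die were worse at admission and improved less. The tested trajectory of CRS-R or FOIS would then start too high and rise too steeply for the cohort as enrolled. A reader would take it as the recovery course of patients admitted to these units, when it is the course of those who lived and were reached at 24 months.

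A separate, smaller problem is that visit number stands in for time. Because two starting points are used, the same visit label covers different times since injury, and one of the between-visit intervals is not the same for all patients.

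**Working it through.** **Denominators.** The article's subgroup sizes reproduce from the single-proportion precision formula n = z²·p(1−p)/d² with z = 1.96.
- MCS: 1.96² × 0.47 × 0.53 / 0.05² = 382.8, so 383 (p = 0.5 gives 384.1; the article has 384).
- UWS: 1.96² × 0.03 × 0.97 / 0.03² = 124.2, so 125, as stated.
- Sum: 384 + 125 = 509. Centre targets: 200 + 200 + 60 + 60 = 520.

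**Complete-row requirement.** As a check, a classical repeated-measures ANOVA was fitted in statsmodels to 10 patients and five visits with one cell missing. It stopped with an unbalanced-data error. The patient must be dropped or a value supplied, and no meaningful CRS-R, FOIS or BMI value exists after death.

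**Complete rows left** = N × (1 − mortality by T4) × (1 − loss among survivors).

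| N | Mortality by T4 (assumed) | Further loss (assumed) | Complete rows |
|---|---|---|---|
| 509 | 42% | 0 | 295 |
| 509 | 52% | 0 | 244 |
| 509 | 42% | 10–20% | 266–236 |
| 509 | 52% | 10–20% | 220–195 |
| 520 | 10% | 0–20% | 468–374 |
| 520 | 20% | 0–20% | 416–333 |
| 520 | 30% | 0–20% | 364–291 |

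The 42% and 52% rows borrow the Introduction's figure for prolonged disorders of consciousness, which has no stated time horizon. The 10–30% rows allow for a cohort that also contains conscious patients.

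**Direction of the error, by illustration.** All values here are assumed. Let b be a standard normal severity factor (higher is better). The T0 score has mean 10 and loads 4 on b. The T0–T1 change has mean 2.0 and loads 1.5 on b. Death falls on the share m with the highest value of −b plus independent standard normal noise. Among survivors the mean of b is φ(z)/[(1 − m)√2], with z the normal quantile at 1 − m.
- m = 20%: 0.280/(0.80 × 1.414) = 0.25; change 2 + 1.5 × 0.25 = 2.4.
- m = 42%: 0.391/(0.58 × 1.414) = 0.48; change 2.7.
- m = 52%: 0.398/(0.48 × 1.414) = 0.59; change 2.9.

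A simulation of 200,000 patients gave 2.37, 2.71 and 2.88, with T0 means among completers of 11.0, 11.9 and 12.3 against 10.0 for all. This shows direction under a link between death and severity. It does not estimate the bias in this study.

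**Two starting points.** Let admission fall t months after injury, 0 ≤ t < 4.
- T1 is at t + 3 (3 to 7 months from injury) and T2 at t + 6 (6 to 10 months).
- T2 to T3 is 12 − (t + 6) = 6 − t, from 6 down to 2 months.
- T0–T1 and T1–T2 are 3 months and T3–T4 is 12 months for everyone.

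Only the T2–T3 interval varies. The end at t = 0 is an outer limit, since these are post-acute admissions.

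**The case against.** The strongest reply is that little depends on these tests. They cover about five variables and are descriptive. The primary and secondary outcomes are analysed by logistic regression, and prediction by machine learning. This stands, and it limits the weight of the point.

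Four stronger readings are tempting, and the documents do not support them.
- *That about half of the baseline data is thrown away, and selectively the sickest half.* The per-visit descriptive statistics are not restricted to completers, and T0 data also enter the regressions and prediction models. Patients leave these tests, not the dataset. The 42–52% figure covers prolonged disorders of consciousness, while entry does not require one. No figure in the article shows that those lost are the worst.
- *That the paired two-visit tests share the fault.* They lose only patients absent at one of the two visits. A T0–T1 comparison keeps someone who dies after T1.
- *That assessing function only after consciousness returns empties further rows.* The Discussion does say "Only after the consciousness recovery, some measures of functioning, including motor and cognitive impairment, activity, and participation were applied". In Table 1, however, such measures are mostly taken at some visits only: Trunk Control and Ashworth at T0–T2, Galveston at T1–T2, cognition and community integration at T3–T4. They mostly fall outside the five-visit tests.
- *That the two starting points invalidate the ANOVA or create a spurious T2–T3 change.* They are an openly declared design, and a test with visit as a factor does not need equal spacing. What remains is that the T2–T3 contrast averages over intervals of different length.

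It can also be said that an unseen analysis plan may deal with missing data. That would not settle the matter, because the tests are named here and they cannot use an incomplete row.

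Finally, a mixed model does not define a score after death and can implicitly extrapolate beyond it. This is right, and the fix has to state it.

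**Conclusion.** The point holds for a secondary, descriptive analysis. As written, the three tests compare T0 to T4 only among patients seen at all five visits, so early change is conditioned on being alive and reached at 24 months. Recovery is probably overstated for CRS-R, FOIS and similar functional measures if death goes with a worse state. For BMI and device status no direction is claimed.

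The loss ranges from 42–52% (244–295 of 509 left, before any telephone non-response) if the cited mortality applied by T4, to a smaller one if many patients are conscious (291–468 of 520 left under the assumed 10–30% mortality and 0–20% further loss). Which end applies cannot be told from the article. If death is scored as a GOS-E level, that variable could keep the deaths, but the article does not say so and it would not help the others.

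The varying T2–T3 interval (outer limits 2–6 months) is a separate and lesser fault. The article itself names shorter time since the event as a possible predictor of recovering consciousness, so it is worth modelling. The choice of tests does not affect the primary logistic regressions.

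**What to change.** In Statistical Analysis, replace the three tests for five-visit variables as follows.
- Use linear or ordinal mixed models for scores, and GEE or mixed logistic models for binary measures, with every available visit from every enrolled patient.
- Enter actual time since injury at each assessment, either as the time variable or as a covariate beside visit.
- Print the number dead at each visit next to each trajectory, and label the trajectory as conditional on being alive.
- For GOS-E, keep death as its own level so that deaths stay in the analysis.

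The paired two-visit tests can stay if each reports how many pairs it used.

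The cost is a change of wording and slightly more analysis work. No new data should be needed, since onset and visit dates are inherent in the design, and the named software has mixed-model and GEE procedures. One limit remains: scores after death stay undefined, so the survival-conditional reading must be stated wherever these results appear.

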### Outcome Measures

The primary outcome is the functional recovery, given by the achievement of a moderate functional disability (GOS-E>4), whereas the independent variables will be the severity of the patients' clinical state at admission. For those patients who will remain in DoC at discharge from the IRU, given that the GOS-E does not allow accurate discrimination between different states of consciousness, consciousness improvement will be considered. The improvement will be stated as the transition from one state of consciousness to a higher one (based on the CRS-R assessment). These outcomes will be measured both at short-term evaluations, T1 and T2, and at long-term ones, T3 and T4.

Secondary outcomes will be considered at the same time points. They are (1) tracheostomy decannulation success and its timing and (2) complete oral feeding recovery corresponding to FOIS score ≥4. Additionally, at follow-up time points (T3 and T4), the level of participation, using the CIQ scale, and the subjective and caregiver perceived QoL, using the QoLibri, will also be considered as secondary outcomes.

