
To identify a profile of sABI patients based on a multiparameter assessment, the combination of the many recorded measures can be best exploited by machine learning analysis. The applicability of these solutions is also supported by the consideration that, with the only exception of the neurogenetic assessment, all the clinical and instrumental variables selected in this study are easily exportable to other clinical realities because of their low cost and high feasibility. Specifically, in this context, an accurate prediction is relevant both for planning a personalized rehabilitation pathway and for communication with relatives and caregivers. For these reasons, the ultimate goal of this study is to reliably predict the main recovery milestones, including the achievement of a consciousness recovery, tracheostomy decannulation, complete oral nutrition, functional independence, and the recovery of participation in familiar and social contexts. Differently from what is most often found in the existing literature, the aim of these analyses will be two-fold, addressing both the success in the achievement of these goals and their timing. The candidate predictors of these solutions will be selected from a comprehensive evaluation of sABI patients, including the biomarkers obtained from genetic sequencing and quantitative and qualitative EEG features.

Finally, another innovative point will be the comparison of these models with the clinical assessment performed by a multidisciplinary team within the first 2 weeks from admission. This comparison will represent a first step in the direction of computational tools translation into clinical practice.

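### Logistic regression is the only model stated for the two-step predictor analysis of the secondary outcomes, and it does not fit decannulation timing or the undichotomised CIQ and QoLibri scores

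*Protocol article*

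**What the plan says.** Under Outcome Measures, the protocol article lists as secondary outcomes "tracheostomy decannulation success and its timing" and "complete oral feeding recovery corresponding to FOIS score ≥4", at the same visits as the primary outcome (T1 to T4). For the phone follow-up visits, T3 and T4, it adds that "the level of participation, using the CIQ scale, and the subjective and caregiver perceived QoL, using the QoLibri, will also be considered as secondary outcomes". No cut-off is given for either scale.

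Under Statistical Analysis, one process covers all of these: "For the secondary outcomes, a two-step process constituted on univariate analyses adjusted by age and sex and multivariate analysis will be performed". The next sentence names the model for both steps: "univariate analyses, adjusted by proper confounders, and multivariate analyses will be performed using logistic regressions". No secondary outcome is excepted.

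The same section also gives paired tests for numeric scales at two visits. Its machine-learning paragraphs compare linear and logistic regression with other algorithms, scored by accuracy, F1, root mean square error (RMSE) and the determination coefficient. The Discussion describes the aim of the prediction work as "addressing both the success in the achievement of these goals and their timing". The Introduction notes that "long-term mortality is high (42–52%) in patients with prolonged DoC".

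**The concern.** An outcome and its model should match in type. Here the article names the model, and it matches only some of the outcomes assigned to it. Followed as written, the predictor analysis gives no estimate of what speeds or delays decannulation, although timing is part of a named outcome. CIQ and QoLibri would have to be cut at a point that nobody has fixed in advance, which loses information and leaves the cut open to choice after the data are seen.

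Timing also raises the question of death. A patient who dies with the tube in place never has a decannulation time, and a patient still cannulated at the last contact has only a lower bound. A method that needs an observed time must drop both groups or invent a value for them. The Discussion intends these predictions for planning rehabilitation and for talking to relatives, so an analysis restricted to patients who reached the milestone would mislead the people it is meant to inform.

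**Working it through.** The article states no figure for any secondary outcome (its sample size rests on GOS-E), so there is none to reproduce. The check sets each outcome against the stated methods and then illustrates how much the treatment of death can matter.

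**1. Outcome type against stated method**

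| Secondary outcome | Type as defined | Logistic predictor model | Other stated method |
|---|---|---|---|
| Decannulation success | yes/no | fits | classification, machine-learning step |
| Decannulation timing | time to event | does not fit | regression scored by RMSE; no censoring or death |
| FOIS ≥4 | yes/no | fits | classification, machine-learning step |
| CIQ at T3, T4 | score, no cut-off | does not fit without a cut | paired test T3 v T4; linear regression |
| QoLibri at T3, T4 | score, no cut-off | does not fit without a cut | paired test T3 v T4; linear regression |

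**2. Why a yes/no model carries no timing.** Suppose two groups (assumed) each have 70% decannulated by T1, one early in the interval and one late. The odds at T1 are 0.70/0.30 = 2.33 in both, so the odds ratio is 1. Separate models at T1 to T4 give four cross-sections and no single timing estimate.

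**3. Why the prediction step does not fill the gap as stated.** RMSE is the square root of the mean of (observed time − predicted time)². The determination coefficient also needs the observed time. For a patient who died with the tube in place or still has it, that time does not exist. Accuracy and F1 score a class, not a time.

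**4. Illustration of the effect of death (assumed values).** Take constant, independent hazards over 24 months. Let Q be the probability of decannulation if nobody died, and D the probability of death. The cumulative hazards are a = −ln(1−Q) and b = −ln(1−D), and the proportion actually decannulated is

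a/(a+b) × [1 − exp(−(a+b))].

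Worked case, Q = 0.70 and D = 0.42: a = 1.204, b = 0.545, a+b = 1.749, exp(−1.749) = 0.30 × 0.58 = 0.174. The result is (1.204/1.749) × 0.826 = 0.569.

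| D | Q = 50% | Q = 70% |
|---|---|---|
| 10% | 47.7% | 67.1% |
| 20% | 45.4% | 64.1% |
| 42% | 39.8% | 56.9% |
| 52% | 36.9% | 53.2% |

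Treating deaths as ordinary censoring would report Q itself. The overstatement runs from 50 − 47.7 = 2.3 points to 70 − 53.2 = 16.8 points. Only the 42% and 52% come from the article, and there they describe prolonged disorders of consciousness. The other mortality values and both decannulation rates are assumptions.

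**The case against.** The strongest reply is that the plan offers more than logistic regression. A reader might infer that CIQ, QoLibri and timing have no other stated analysis at all, and the article does not support that. Paired tests for numeric scales suit CIQ and QoLibri, which are measured at exactly two visits, and linear regression with RMSE could predict their scores. This stands, and it narrows the point on the scales to the two-step predictor models.

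Second, the Discussion's sentence on timing belongs to the machine-learning work, so the logistic step is tied to timing only through the outcome definition. That is also right, but the definition is enough, because the two-step process covers the secondary outcomes without exception.

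Third, random forests and neural networks can be fitted with censoring-aware objectives, and a discrete-time hazard model is itself usually a logistic model on person-periods. Both are true. The article rules out neither, but it states neither, and the metrics it names cannot score a censored time.

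Fourth, a reader might infer that patients without a tracheostomy, or already at FOIS ≥4 at admission, will be counted in the success analyses. The article is silent here. Success and recovery presuppose a tube or a deficit, and the at-risk definition is commonly left to a full plan. The same applies to the handling of deaths taken alone. It matters here because a timing analysis cannot be chosen without it.

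Finally, a reader might apply 42–52% mortality to the whole cohort and obtain a dramatic contrast. For example, take 100 patients with a tracheostomy, of whom 45 die cannulated, 40 are decannulated and 15 live with the tube. Success is then 40/100 = 40%, or 40/55 = 73% if deaths are dropped. That is an assumed extreme. The quoted mortality is long-term and specific to prolonged disorders of consciousness, whereas the cohort enrols patients with and without them.

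**Conclusion.** The concern holds in this limited form: the model named for the two-step analysis does not fit three of the quantities assigned to it (decannulation timing, CIQ and QoLibri). It does fit decannulation success and FOIS ≥4. For the two scales, the linear step elsewhere in the plan is a partial remedy. For timing, no method or metric as stated deals with patients who die or remain cannulated.

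Severity is moderate. These are secondary outcomes of an observational cohort, and the binary primary outcome is untouched. The mismatch itself rests on the text alone. The size of the death effect, about 2 to 17 points in the illustration, rests on assumed mortality and decannulation rates with constant, independent hazards, and it should not be read as an estimate for this cohort.

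**What to change.** - **Decannulation success and FOIS ≥4:** keep logistic regression, restrict it to patients at risk at T0 (tube present; FOIS below 4), and state how deaths before the visit count.
- **Decannulation timing:** measure from T0 and use a time-to-event model with death as a competing event: cumulative incidence curves plus cause-specific Cox regression. If only the visit is known, use a discrete-time competing-risks model over T1 to T4. Table 1 already schedules medical devices at T0 to T4. T3 is dated from onset and enrolment is within 4 months of it, so T3 falls between 12 − 4 = 8 and 12 months after T0. The model should allow for unequal intervals.
- **Timing predictions:** score them with a censoring-aware measure, such as a c-index or Brier score adapted for censoring, instead of RMSE and the determination coefficient.
- **CIQ and QoLibri:** use linear or ordinal regression in patients able to respond, and report the numbers dead or unable to respond alongside.

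The cost is revised analysis wording and a few more models, largely on data already scheduled. The one extra demand on the sites is recording decannulation dates (and dates of death), unless the visit-level model is used.
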